## Introduction

Atrial fibrillation (AF) is one of the commonest arrhythmias observed in clinical practice [1]. Globally, the incidence of AF is rising. The thromboembolic complications of AF can lead to significant disabling consequences for patients, including transient ischemic attack, stroke, and pulmonary embolism. Early recognition of AF in general practice can lead to early intervention with managing the risks of these complications.

Current guidelines on the management of AF by the National Institute for Health and Care Excellence (NICE) advise identifying and managing the underlying causes of AF, treating the arrhythmia, and assessing and managing the risk of stroke in these patients [2]. Risk of stroke is determined by the CHA_2_DS_2_-VASc (Congestive heart failure, Hypertension, Age, Diabetes, previous Stroke/transient ischemic attack–VAScular disease) assessment tool [3], which guides the practitioner on commencing anticoagulation treatment to manage this risk. The risk of starting a patient on anticoagulation is assessed using the HAS-BLED (Hypertension, Abnormal renal/liver function, Stroke, Bleeding history or predisposition, Labile international normalized ratio, Elderly, Drugs/alcohol concomitantly) score, assessing for major bleeding risks [4].

Anticoagulation therapy aims to reduce the risk of thromboembolic events. This has been achieved using warfarin (a vitamin K antagonist) for many years. The introduction of direct oral anticoagulants (DOACs) such as apixaban and rivaroxaban to clinical practice has changed how AF is managed in clinical practice [5]. In comparison to warfarin, DOACs are observed to have similar or better mortality and vascular outcomes [6]. They have the added benefit of requiring no monitoring, as opposed to warfarin use [7]. Though studies have highlighted that increased number of patients in clinical practice are receiving treatment for AF [8], whether they are managed according to national or local guidelines is unclear. Better understanding of current management trends of AF in population will guide practitioners on how best to employ interventions in clinical practice to increase awareness of AF and early recognition.

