The aim of this study is to understand the disease and prescribing trends related to AF in general practice. We also aim to develop a system to monitor practice-level indicators for AF of the same trends and evaluate the usability of this system. The primary objective of this study is to investigate if people with newly diagnosed AF treated with DOACs versus warfarin have any difference in stroke or all-cause mortality in long-term follow-up. The secondary objectives of this study are to develop an AF dashboard as an intervention method at a practice level and to evaluate the usability of the AF dashboard.

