## Methods

### Study Design

This study combines qualitative and quantitative methods and therefore, was planned as a mixed method study [9-11]. It was run within the Oxford Royal College of General Practitioners Research and Surveillance Centre (RCGP RSC) sentinel network of general practices. The mixed method study was conducted in 2 phases. Phase 1 was a quantitative analysis of AF data. We conducted a repeated cross-sectional study to identify those patients diagnosed with AF during 2009-2019 and identified current therapeutic management of their AF. Phase 2 involved development and evaluation of a dashboard for monitoring data quality for AF. The dashboard provides the general practices in the RCGP RSC sentinel network an access to quality indicators related to AF management that are updated weekly.

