#### Exposures and Outcomes

We considered the exposure as continuous anticoagulant prescription for the first time after receiving an AF diagnosis. Although almost all anticoagulant prescriptions in the United Kingdom are issued from primary care if an anticoagulant is started in a hospital, we measured exposure from the first general practice prescription. We excluded patients who had an interval of greater than 90 days between anticoagulant prescriptions.

Outcomes are first records of stroke and all-cause mortality based on previously published Read codes [16,17] Stroke was included regardless of etiology, an approach used in other studies [18,19]. Study participants were followed for stroke and all-cause mortality till the end of the study period.

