#### Covariates

We included variables likely to be used as indicators in prescribing anticoagulants: age-band, gender, and deprivation reporting Index of Multiple Deprivation (IMD) quintile. IMD is a national measure of socioeconomic status, which can be derived at an individual level from first part of postcode. We adjusted for comorbidities from that part of the stroke risk score (CHA_2_DS_2_-VASc), namely, heart failure, hypertension, stroke or transient ischemic attack, and myocardial infarction or peripheral vascular disease at baseline. We also included smoking status as a covariate.

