### Statistical Analysis

Analysis of data extracted from general practice CMR was carried out using the statistical software R. We studied the influence of the anticoagulation regimen by evaluating the cause-specific hazard ratio and the subdistribution hazard ratios of both events. Additionally, we estimated cumulative incidence for both events by direct regression, utilizing the inverse of the probability of censoring weights method [15] with time-varying effects [20]. We will report and interpret both cause-specific and subdistribution analyses. The cause-specific hazard ratio is often interpreted as estimating etiological association, estimating associations between covariates, and the rate at which events occur in those participants who are event-free. The cause‐specific hazard ratio can be interpreted as a rate ratio. Whenever the proportional hazards assumption was violated, we interpreted all hazard ratios as time-averaged effects.

We will determine the (adjusted) incidence and prevalence of AF for each year along with the proportion of incident and prevalent cases treated with nothing, antiplatelet medications only (eg, aspirin), and anticoagulant therapy (warfarin/types of DOACs). We will also determine the number of strokes, transient ischemic attacks, deaths, and bleeds in the incident and prevalent cases per year.

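### The stated adjustment set for DOAC versus warfarin leaves out calendar year of first prescription, so era differences can appear as a drug effect, in either direction

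*Protocol article*

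**What the plan says.** The Introduction of the protocol article sets the primary objective: whether "people with newly diagnosed AF treated with DOACs versus warfarin have any difference in stroke or all-cause mortality in long-term follow-up". The Study Design section takes in patients over a decade, aiming to "identify those patients diagnosed with AF during 2009-2019".

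The Introduction also places the two drug classes in time. Of stroke prevention it says: "This has been achieved using warfarin (a vitamin K antagonist) for many years". Of the newer drugs it says: "The introduction of direct oral anticoagulants (DOACs) such as apixaban and rivaroxaban to clinical practice has changed how AF is managed in clinical practice".

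Under Exposures and Outcomes, exposure starts at the first general practice prescription, and follow-up has one calendar end: "Study participants were followed for stroke and all-cause mortality till the end of the study period".

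The Covariates section begins: "We included variables likely to be used as indicators in prescribing anticoagulants: age-band, gender, and deprivation reporting Index of Multiple Deprivation (IMD) quintile". It then adds heart failure, hypertension, stroke or TIA, myocardial infarction or peripheral vascular disease, and smoking. No calendar variable is listed.

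The Statistical Analysis section plans cause-specific and subdistribution hazard ratios, and cumulative incidence by direct regression, "utilizing the inverse of the probability of censoring weights method". Year appears there only in descriptive annual counts. No section restricts, matches or stratifies the drug comparison on start date.

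**The concern.** On the article's own account, the year in which a patient starts treatment largely governs which drug class is likely. The section's stated rule is to include variables likely to guide prescribing, and start year fits that rule better than most of the variables listed.

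Start year can also be linked to the outcome. Stroke and death rates, the mix of patients given anticoagulants and the completeness of coding may all change over ten years. The Case Ascertainment section itself reports that pay-for-performance has recently improved AF data quality. A variable tied to both exposure and outcome, and left out of the model, confounds the contrast.

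This affects the study's main comparison. The bias does not shrink as the database grows, and it can be as large as a modest drug effect.

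**Working it through.** The article states no sample size, event rate, uptake curve or trend for Phase 1, so there is no figure to reproduce. The check asks what the stated model returns when the drug has no effect.

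**From the article:** diagnoses 2009-2019; one end date for all; no calendar term in the model.

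**Assumed:**
- Starts are uniform over ten years from 2009, with follow-up ending at 2019.4.
- DOAC share rises linearly from 0 in 2012 to 90% in 2019.
- Stroke hazard is 0.015 per year and death hazard 0.05 per year in 2009.
- Both hazards are multiplied by (1 + trend)^(start year − 2009).
- The true hazard ratio is 1.

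**Step 1: separation in time.** Mean start year is 2012.8 for warfarin and 2016.7 for DOAC, a gap of 3.9 years. Median potential follow-up is about 7.0 and 2.4 years.

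**Step 2: rough size.** A crude rate ratio should be near (1 + trend)^3.9:
- 2% fall: 0.98^3.9 = 0.92
- 4% fall: 0.96^3.9 = 0.85
- 2% rise: 1.02^3.9 = 1.08

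**Step 3: the planned estimator.** A Cox cause-specific model for stroke compares patients at the same time since start, which narrows the gap a little. In a simulation of 6,000,000 patients per scenario (standard error about 0.005):

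| Trend per start year | HR without start year | HR stratified by start year |
|---|---|---|
| none | 0.99 | 0.99 |
| −2% | 0.94 | 1.00 |
| −4% | 0.87 | 0.99 |
| +2% | 1.06 | 1.00 |

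For the 2% rise, separate runs gave 1.06 to 1.08. Stratified results across the runs under this uptake lay between 0.99 and 1.03, which is 1 within simulation error.

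**Step 4: other uptake dates.** With DOAC uptake starting in 2011, 2012 or 2013 and reaching 85% in 2019, falls of 2% to 5% a year give hazard ratios of 0.84 to 0.95. Stratifying by start year gives 0.97 to 1.02.

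**Step 5: censoring weights (conditional).** With one end date, censoring time equals end date minus start date, so it is tied to drug through start year. Suppose the weights came from one censoring curve pooled over both drugs. With no trend and no drug effect, the DOAC/warfarin ratio of stroke cumulative incidence would be about 0.73 at 3 years and 0.56 at 5 years. Drug-specific weights give about 0.99 and 1.00. With a 4% fall, drug-specific weights alone still leave about 0.88 at 3 years, so they do not replace start year in the outcome model.

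**The case against.** **The article is a condensed account, and a fuller plan may exist.** This is a fair answer on the censoring model. A reader might infer that the weights ignore drug and calendar time, but the text names only the method and not what enters it. The 0.73 and 0.56 ratios therefore describe a choice the article does not make, and they are no evidence of error. The answer does not carry over to the covariates, because the article sets out that list and start year is not on it.

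**Unequal follow-up is not in itself a bias in every estimator.** A reader might infer that it distorts all the hazard ratios. It does not: with no era trend and proportional hazards, the cause-specific hazard ratio stays at about 1. Unequal follow-up matters for pooled weights. It also matters where non-proportional hazard ratios are read as time averages, since the average depends on the follow-up available.

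**The direction is not documented.** A reader might infer a spurious DOAC benefit. No section gives a trend in stroke or death. The one era change reported is better AF recording; if stroke recording improved too, recorded rates would rise and the bias would run against DOACs.

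**The listed covariates absorb part of the era effect.** This is true of any part due to measured age, comorbidity or smoking, and the simulations do not model it. Changes in background rates or recording would remain.

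**Conclusion.** The point holds for the covariate list. The stated model compares a long-established drug with a later one over a decade, without start year, and nothing else in the article controls for it. Under the assumed uptake, a trend of 2% to 4% per start year moves a null stroke hazard ratio to about 0.94 or 0.87 if rates fall. A 2% rise moves it to about 1.06 to 1.08. With no trend there is no bias. These sizes rest on the assumed uptake and trends and show what is possible, not what happened in this dataset. The censoring weights are a matter to specify and not a demonstrated error.

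**What to change.** - Add calendar year of first prescription, as yearly strata or a flexible term, to the cause-specific, subdistribution and direct-regression models for DOAC versus warfarin.
- Add a sensitivity analysis restricted to start years in which both drug classes were prescribed in the network.
- State how the censoring weights are estimated, and let them depend on drug and start date.
- Report cumulative incidence only to a horizon that both groups reach.

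No new data are needed, since the first prescription date already starts the exposure. The article reports that the Phase 1 analysis was completed in December 2019, so the cost is a rerun with one more covariate. Some precision is lost because start year is correlated with drug, and with yearly strata the warfarin-only years no longer inform the contrast.

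### All-cause mortality is one of two outcomes in the DOAC versus warfarin comparison, but the comorbidities adjusted for are all stroke-score items, with no non-cardiovascular disease, frailty or general comorbidity measure

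*Protocol article*

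**What the plan says.** The Introduction states the primary objective as whether people with "newly diagnosed AF treated with DOACs versus warfarin have any difference in stroke or all-cause mortality in long-term follow-up". Exposures and Outcomes repeats the pair: "Outcomes are first records of stroke and all-cause mortality based on previously published Read codes".

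The Covariates section gives the selection rule, "We included variables likely to be used as indicators in prescribing anticoagulants", and then the list:

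- Demographics: "age-band, gender, and deprivation reporting Index of Multiple Deprivation (IMD) quintile".
- Comorbidities: "We adjusted for comorbidities from that part of the stroke risk score", and then "namely, heart failure, hypertension, stroke or transient ischemic attack, and myocardial infarction or peripheral vascular disease at baseline".
- Lifestyle: "We also included smoking status as a covariate".

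No separate set is given for death. Statistical Analysis plans cause-specific and subdistribution hazard ratios for both events, and a direct regression for cumulative incidence that uses inverse-probability-of-censoring weights.

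**The concern.** Drug choice was not randomised, so the adjustment set has to cover what influences both the choice of drug and each outcome. The stroke score guides whether to anticoagulate. The contrast here is which anticoagulant was used, and one outcome is death from any cause. In an older population much of that risk comes from cancer, chronic lung disease, dementia and frailty, and none of these is listed.

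The Introduction itself names a practical difference between the drugs: warfarin needs monitoring and DOACs do not. It is plausible that a prescriber would weigh a patient's general condition when choosing between them. If so, part of any mortality difference could reflect who received which drug.

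The consequence is not confined to mortality. Death competes with stroke, so a distorted difference in death also moves the stroke subdistribution hazard ratio and the stroke cumulative incidence. For example, if frailer patients were on warfarin, more of them would die before a stroke could be recorded. All else equal, warfarin's stroke incidence would then look lower.

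**Working it through.** **Covariates against outcomes.** The article gives no event count, effect size or cohort size for Phase 1, so there is no figure of the plan's to reproduce. The check compares the list with the outcomes.

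- Heart failure, hypertension, stroke or transient ischaemic attack, and vascular disease are all components of the stroke score as the Introduction spells it out. The word *namely* closes this list.
- Age-band, gender, deprivation quintile and smoking carry information on death from any cause. They adjust for general prognosis in part.
- Cancer, chronic lung disease, dementia, frailty and a general comorbidity index do not appear.

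**Other safeguards in the text.** The weights in Statistical Analysis are for censoring, which does not balance the drug groups at baseline. No treatment-propensity method, negative control or sensitivity analysis for unmeasured confounding is described. The Discussion addresses missing data, not residual confounding.

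**Illustration of size, on assumed inputs.** Let a share p_W of warfarin starters and p_D of DOAC starters be frail, let frailty multiply the death hazard by HR_F, and let the drugs have no effect. Each group's death rate is proportional to 1 + p(HR_F − 1). The apparent DOAC versus warfarin hazard ratio is then

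[1 + p_D(HR_F − 1)] / [1 + p_W(HR_F − 1)].

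With p_W = 0.30, p_D = 0.20 and HR_F = 2.5, this is (1 + 0.20 × 1.5) / (1 + 0.30 × 1.5) = 1.30 / 1.45 = 0.897.

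| Frail: warfarin v DOAC | HR_F = 2 | HR_F = 2.5 | HR_F = 3 |
|---|---|---|---|
| 30% v 25% | 1.25/1.30 = 0.962 | 1.375/1.45 = 0.948 | 1.50/1.60 = 0.938 |
| 30% v 20% | 1.20/1.30 = 0.923 | 1.30/1.45 = 0.897 | 1.40/1.60 = 0.875 |
| 25% v 15% | 1.15/1.25 = 0.920 | 1.225/1.375 = 0.891 | 1.30/1.50 = 0.867 |

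The range is 0.87 to 0.96. If the frailer patients receive DOACs, the reciprocals apply: 1/0.962 = 1.04 to 1/0.867 = 1.15.

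Wider assumptions widen the range. A 5-point gap (25% v 20%) with HR_F = 1.5 gives 1.10/1.125 = 0.98. A 20-point gap (35% v 15%) with HR_F = 3 gives 1.30/1.70 = 0.76.

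The shares should be read as the imbalance left after adjustment for the listed covariates. The formula approximates the rate ratio early in follow-up. Over long follow-up frail patients are depleted by death, and the averaged bias tends to shrink.

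**The case against.** The best defence has four parts.

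1. **Prescribing indicators are a recognised basis for choosing confounders.** A strong predictor of death confounds only if it is also related to drug choice. This stands as a principle. It does not rescue the list, because its disease terms reflect the decision to anticoagulate, and the contrast is between two anticoagulants.

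2. **Prognosis is already adjusted in part.** Age-band, deprivation and smoking all predict non-cardiovascular death, and smoking is a proxy for lung disease and some cancer. This stands. A reader might infer that nothing in the model speaks to non-cardiovascular prognosis, and the list does not support that. What is absent is any non-cardiovascular disease, frailty or overall comorbidity term. The imbalance that matters is what remains after the listed terms, which may be smaller than the shares assumed above.

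3. **Channelling is not documented.** This also stands. A reader might conclude that the mortality result is confounded, or that it favours a particular drug. The article says only that one drug class needs no monitoring. It does not say that prescribers weigh frailty, cancer or dementia, or in which direction. Only possible bias, of unknown sign and size, is supported.

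4. **A journal article condenses, and a fuller plan may adjust for more.** That would excuse silence. Here the covariates are printed as what was included and adjusted for, and the comorbidity list is closed. It is a stated choice.

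It might also be argued that the Abstract gives a different primary aim, guideline-concordant management. The Introduction nevertheless names the DOAC versus warfarin comparison as the primary objective, and Exposures and Outcomes defines its two outcomes.

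**Conclusion.** The point holds in a conditional form. The stated adjustment set leaves avoidable room for residual confounding of all-cause mortality, one of the two outcomes of the primary comparison. Through competing death it does the same for the stroke subdistribution hazard ratio and cumulative incidence. The cause-specific stroke hazard ratio is not affected by that route.

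The size cannot be known from the document. On the main assumed inputs, a true hazard ratio of 1 for death would appear as about 0.87 to 0.96, or about 1.04 to 1.15 if channelling is reversed. A shift of that order could be mistaken for a modest drug effect. The article speaks of studying the influence of the regimen and notes that cause-specific hazard ratios are often read aetiologically, so the risk of over-reading is real.

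It would be tempting to add that, if the estimate moves when more covariates enter, the mortality contrast cannot be interpreted. That does not follow. A change would show that measured confounding had been removed, and agreement would not prove that none remained.

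**What to change.** Add baseline terms for cancer, chronic lung disease, dementia and a frailty or general comorbidity index to the cause-specific, subdistribution and direct cumulative-incidence regressions. Use only codes recorded before the first anticoagulant prescription. There is no treatment-weighting model to extend, so the change belongs in these outcome models.

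In reporting:

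- Show the balance of the added variables by drug.
- Take the fuller model as the main mortality result, with the currently listed set alongside it.
- Describe the mortality contrast as associational and acknowledge residual confounding.

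The cost is extra code lists, a re-run of the models and a small loss of precision. The exact loss cannot be stated, because the Phase 1 cohort size is not given. The article does not say whether these diagnoses were in the May 2019 extract, so a supplementary extract from the same database may be needed. The analysis was completed in December 2019, but the publications were still under review in October 2020, so the change could be made as a revision.

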#### Case Ascertainment

We used Read codes and CTV3 codes used in primary care CMR systems to identify patients with AF. Pay-for-performance (P4P) for chronic disease management has improved data quality related to AF in the recent past [15]. We excluded patients who had a previous stroke and those not on British National Formulary–recommended dose of DOAC. We included patients over 18 years with code for the diagnosis of AF who had been registered at any point between 2008 and 2019.

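### The adjustment list omits diabetes from the stroke score it draws on, includes a stroke history that eligibility has removed, and has no bleeding-specific factor

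*Protocol article*

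**What the plan says.** All references are to the protocol article.

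- **Covariates, criterion.** "We included variables likely to be used as indicators in prescribing anticoagulants: age-band, gender, and deprivation" (the last reported as IMD quintile).
- **Covariates, comorbidities.** "We adjusted for comorbidities from that part of the stroke risk score", followed by a specific list: "heart failure, hypertension, stroke or transient ischemic attack, and myocardial infarction or peripheral vascular disease at baseline". Smoking status is then added.
- **Introduction, stroke score.** CHA2DS2-VASc is expanded as "Congestive heart failure, Hypertension, Age, Diabetes, previous Stroke/transient ischemic attack", plus vascular disease. The abbreviation list gives the same expansion.
- **Introduction, bleeding score.** "The risk of starting a patient on anticoagulation is assessed using the HAS-BLED" score, whose expansion covers hypertension, kidney and liver impairment, stroke, bleeding history, labile INR, older age, and drugs or alcohol.
- **Case Ascertainment.** "We excluded patients who had a previous stroke". TIA is not named in the exclusion.
- **Statistical Analysis.** Cause-specific and subdistribution hazard ratios are estimated by anticoagulant regimen. No other confounding control, such as matching or treatment weighting, is described.

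**The concern.** The Introduction makes DOAC versus warfarin, on stroke and all-cause mortality, the primary objective. Treatment was chosen by prescribers, so the estimate is only as good as the adjustment set. That set disagrees with the rest of the article in two places and falls short of its own criterion in a third.

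1. It cites a score as the source of its comorbidities and then leaves out one comorbidity of that score.
2. It adjusts for a history that the eligibility rule has removed.
3. It sets out to capture what informs anticoagulant prescribing, but lists nothing specific to bleeding, although the article names a bleeding score for that decision.

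The first and third can leave confounding in the primary hazard ratios that the plan could have avoided. The second leaves the reader unsure what the covariate measures. If the exclusion was not in fact applied, it also leaves unclear who was analysed.

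**Working it through.** The article states no effect size, event count or covariate prevalence for phase 1, so there is no figure of its own to reproduce. The first two steps compare text. The last two illustrate size on assumed inputs.

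**Step 1. Stroke score against covariate list**

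| CHA2DS2-VASc component (Introduction) | In Covariates? |
|---|---|
| Heart failure | yes |
| Hypertension | yes |
| Age | yes, in bands |
| Diabetes | **no** |
| Stroke or TIA | yes, but prior stroke is excluded |
| Vascular disease | yes, as infarction or peripheral disease |

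Five of six components are present. After the exclusion, the stroke half of the fifth row is zero for every patient, so that covariate reduces to prior TIA.

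**Step 2. Bleeding score against covariate list**

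| HAS-BLED component (Introduction) | In Covariates? |
|---|---|
| Hypertension | yes |
| Older age | yes, in bands |
| Stroke | nominally; emptied by the exclusion |
| Kidney or liver impairment | **no** |
| Bleeding history | **no** |
| Labile INR | **no** |
| Drugs or alcohol | **no** |

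Four of seven are absent. Labile INR has no useful value before a first anticoagulant prescription, so three absences matter.

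**Step 3. Size of an omitted binary confounder**

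Suppose there is no true drug effect. If the factor has prevalence p_D on DOAC and p_W on warfarin, and outcome hazard ratio HR, the estimated ratio is approximately

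(1 + p_D(HR − 1)) / (1 + p_W(HR − 1)).

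All inputs are assumptions.

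| Factor | p_D | p_W | HR | Arithmetic | Spurious ratio |
|---|---|---|---|---|---|
| Diabetes | 20% | 25% | 1.5 | 1.100 / 1.125 | 0.978 |
| Diabetes | 18% | 24% | 1.7 | 1.126 / 1.168 | 0.964 |
| Renal or bleeding factor | 10% | 20% | 2.0 | 1.100 / 1.200 | 0.917 |

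Swapping the arms gives the reciprocals: 1.023, 1.037 and 1.091. For a wider range on diabetes, take 20% in one arm, 22% to 30% in the other, and HR 1.25 to 2.0. The ratio then runs from 1.055/1.050 = 1.005 to 1.300/1.200 = 1.083.

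These are marginal figures. Diabetes and renal disease plausibly correlate with age, heart failure, hypertension and vascular disease, which are adjusted for, so the bias left in the fitted model may be smaller.

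**Step 4. Banded age (secondary)**

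Assumptions: normal ages with SD 10, means 73 and 75 in the two arms, and a hazard that doubles every 8 years. I took the hazard ratio within each band and averaged the log ratios with inverse-variance weights.

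| Bands | Spurious ratio, by direction |
|---|---|
| Under 65, 65-74, 75 and over | 0.940 or 1.064 |
| 10-year bands | 0.983-0.986 or 1.014-1.017, by where the cuts fall |
| 5-year bands | 0.996 or 1.004 |

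The result depends almost wholly on the band limits, which the article does not give.

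**The case against.** The strongest reply is that most of this is wording.

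- **Subset of the score.** The phrase introducing the comorbidities is garbled and may mean a chosen part of CHA2DS2-VASc, in which case diabetes was left out on purpose. That is possible, but diabetes is the only comorbidity in the article's expansion that was dropped, and no reason is given. The point stands.
- **Stroke or TIA is simply the score's label.** After the exclusion the term indicates TIA, still varies, and biases no estimate. That is right. A reader might infer that the covariate is empty, but TIA is not excluded. What stands is an inconsistency to reconcile.
- **Bleeding risk.** A reader might infer that no bleeding-risk item is adjusted for. That goes too far, because hypertension and age are HAS-BLED components. The prescribing criterion is also attached grammatically to age, sex and deprivation. HAS-BLED is tied to starting anticoagulation, not to choosing between a DOAC and warfarin, and the comparison is among treated patients. So this is a gap against the criterion, not a flat contradiction. That bleeding or renal history influences the choice of drug is plausible, but it is a judgement and not something the article says.
- **Age bands.** Banding contradicts nothing in the article, and its limits may properly sit in a fuller document. I accept this and keep age as secondary.
- **Size.** It is tempting to say that the residual confounding matches the drug effects of interest. The article states no effect size, so that comparison cannot be made.

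**Conclusion.** The concern holds in three parts of unequal weight.

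1. **Diabetes** is the firmest. It is an unexplained omission from the score the list cites, within the only confounding control described for the primary comparison.
2. **Prior stroke** is a real conflict between Case Ascertainment and Covariates. It does no numerical harm if the exclusion was applied, and nothing in the article suggests otherwise.
3. **Bleeding-specific factors** (bleeding history, kidney or liver impairment, drugs or alcohol) are absent from a list meant to reflect prescribing indicators.

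On the assumed inputs above, diabetes shifts the hazard ratio by about 2-4% and a renal or bleeding factor by about 8%. The latter needs a twofold difference in prevalence and a hazard ratio of 2.0, neither of which the article supports or rules out. Both figures are before any allowance for correlation with adjusted covariates. Age banding adds roughly 6% with three wide bands and under 2% with 10-year or finer bands.

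**What to change.** - Add diabetes at baseline to the adjustment set of the primary models.
- Reconcile the two sections. If previous stroke was excluded, relabel the covariate as prior TIA. If it was not, correct the eligibility statement.
- Add the bleeding-specific items recorded before the first anticoagulant prescription: bleeding history, kidney and liver disease, alcohol, and interacting drugs such as antiplatelets. Do this at least as a sensitivity analysis beside the primary model, or state why they are left out.
- State the age-band limits, or model age as a continuous variable with a flexible term.

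**Cost.** The Results section reports phase 1 extraction complete in May 2019, analysis complete in December 2019 and papers under review in October 2020, so this means rerunning a finished analysis. Adding diabetes should be cheap if its codes were extracted. The bleeding-specific items need a check first. The article plans yearly counts of bleeds and an antiplatelet-only treatment group, but neither shows that bleeding history or co-medication before the first prescription was extracted, and renal codes are not mentioned.
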